**Table 2: Examples of results, under different observed results**

| **Proportion failing in surgery arm** | **Proportion failing in epilation arm** | **Difference in proportions** | **95% CI for difference** | **Conclusions** |
| --- | --- | --- | --- | --- |
| 0% | 16% | 16% | 13.1%-19.0% | Inferior |
| 1% | 15% | 14% | 11.0%-17.0% | Inferior |
| 2% | 14% | 12% | 9.0%-15.0% | Inconclusive |
| 3% | 13% | 10% | 6.9%-13.1% | Inconclusive |
| 4% | 12% | 8% | 4.9%-11.1% | Inconclusive |
| 4.5% | 11.5% | 7% | 3.9%-10.1% | Borderline non-inferior |
| 5% | 11% | 6% | 2.9%-9.1% | Non-inferior |
| 6% | 10% | 4% | 0.9%-7.1% | Non-inferior |
| 7% | 9% | 2% | -1.1%-5.1% | Non-inferior |
| 8% | 8% | 0% | -3.1%-3.1% | Non-inferior |

*e) Primary analysis*

Our primary analysis will be a modified intention to treat (ITT) analysis, which will include only those individuals who were seen at least once.

*Justification for using modified ITT:*

In a trial comparing two drug treatments a per-protocol analysis would be used to try to determine the ‘true’ effect of the drug treatment (excluding for example issues of drug compliance), by only analysing the participants who follow their treatment allocation. However, it is not appropriate in the present study, which compares a one-off treatment (surgery), in which all participants follow their treatment allocation, with a repeated treatment (epilation), in which participants may not adhere. Therefore, a per-protocol analysis would require the comparison of all participants in one arm with a biased selection from the other arm. The per-protocol analysis would require exclusion of individuals not epilating in the epilation arm. However, some of these individuals may have epilated once or twice and found the lashes not to recur, thus obviating the need to epilate. These people are treatment successes and it would be wrong to exclude them from the analysis.

A standard intention to treat (ITT) analysis includes all individuals whether or not they adhered to treatment, i.e. all individuals are included in the analysis irrespective of whether they were followed-up. The benefit of an ITT is that it eliminates potential bias of differential loss to follow-up. However, in a non-inferiority trial, failure to follow people up, biases towards non-inferiority and type I error. Therefore, in order to prevent bias towards non-inferiority, the primary analysis included only those individuals who were seen at least once, i.e. a modified intention-to-treat analysis.

*f) Secondary analyses*

1. **Time-to-first-failure:** The time-to-first-failure will be analysed with Cox regression analysis, comparing failure rates in the two trial arms.

*g) Subgroup analyses*

The effect of the intervention on failure will be stratified by presence of:

1. Entropion at baseline
2. Conjunctivilisation at baseline

For each analyses, we will test for effect-modification by strata

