**B: Trial Follow-up Phase**

1. **7-10 day follow-up for surgical patients**

Team members

Nurse

Driver 2, if patient fails to attend for follow up

1. Find appropriate patients according to suture removal lists from each trial.
2. Record post operative examination on new form for patient
3. Double check that this patient is from trial 2 and therefore has silk (BLACK) sutures.
4. Remove all sutures.
5. Record removal of sutures on masterlist E5
6. Give patient further instructions

Masterlist E5

| Unique identifier | Name | Date of suture removal | Eye of suture removal | Early post operative findings |
| --- | --- | --- | --- | --- |
|  |  |  |  |  |
|  |  |  |  |  |
|  |  |  |  |  |

Examination

1. Are/is there:
   1. Discharge
      1. Purulent
      2. Non-purulent
   2. Obvious granuloma (do NOT evert lid)
   3. Bleeding
   4. Early recurrence
      1. Count eyelashes and record
   5. Skin infection / cellulitis
2. Is further surgery being planned?
   1. When?
   2. Where?

Procedure if early recurrence is identified

Either:

1. Operate immediately, if suitably trained surgeon is present
2. Refer to Bahir Dar for urgent re-op
3. Refer to another local surgical campaign, if there is capacity and a suitably trained surgeon.

Failure to present at 7-10 follow up

1. Is this due to:
   1. Death
   2. Travelled
   3. Unknown
2. Driver and suture removal nurse to take all possible steps to find patient or arrange for their presentation as soon as possible for suture removal.

Late complications

If patient re-presents between the 7-10 day follow up and the 3 month follow up, record reason and presence/absence of any of the above complications and follow procedure above.

1. **6 month follow up**

Team

Field Co-ordinator with SR assistance

Driver 1

Assistants

Aims

Full examination and photography

Swabs

1. **One year follow up**

Team

SR

Field co-ordinator

Assistants

Driver 1

Aims

Full examination and photography

Questionnaire

Visual acuity

Swabs

1. **18 month follow up**

Team

Field co-ordinator with SR assistance

Driver 1

Assistants

Aims

Full examination and photography

Swabs

1. **Two year follow up**

Team

SR

Field co-ordinator

Assistants

Driver 1

Aims

Full examination and photography

Swabs

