**Studies on the Management of Trachomatous Trichiasis**

**Analytical Plan for Trial 2: Randomized controlled trial of immediate surgery vs. epilation for Minor Trichiasis**

**1. Participant flow**

*a) Eligibility, enrolment and follow-up*

The following will be shown by trial arm in a flowchart following CONSORT guidelines for non-inferiority trials (JAMA 2006: 295:1152-1160): Numbers eligible, consenting to take part, randomized, and who received the intended treatment. The numbers still in follow-up, censored, defaulting, and permanently lost-to-follow-up respectively at each visit will also be shown by arm. Reasons for declining to take part, not having surgery, or discontinuing follow-up will be summarized by arm.

*b) Censoring*

Patients in both arms will be considered as failures and immediately censored when they present with 5+ lashes in the trial eye. In addition, patients who present having had surgery (or repeat surgery) on the trial eye from other providers will be considered as failures and immediately censored.

1. **Description of baseline data**

The following characteristics of participants at baseline will be tabulated by arm:

- 1. Socio-demographic factors: age, sex, literacy, ethnic group.
  2. Behavioural factors: epilation habits, whether surgery has previously been offered, reasons for not having surgical treatment previously.
  3. Clinical status: trichiasis, entropion, inflammation, conjunctivilisation of lid margin, corneal scarring, evidence of epilation, visual acuity, symblepharon.

The distributions of these variables by treatment arm will be compared, to assess whether there is imbalance at baseline in these potential confounding factors.

1. **Primary outcome**

*a) Definition*

The primary outcome measure will be the proportion of participants with 5 or more lashes touching the eye on one or more follow-up visits. Lids with eyelash stubs which are not in contact with the eye will not be considered a treatment failure.

*b) Justification of primary outcome measure*

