Statistical analyses will calculate the difference in proportion failing in the two arms, and 95%CI for this difference using exact methods. Non-inferiority of epilation will be shown if the upper two-sided 95%CI around the estimated difference in proportions is below 10%. Blinded analyses conducted at the end of the trial showed an overall failure rate of 8%. Table 2 shows conclusions for different assumptions of the proportion failing in the surgery and epilation arm respectively. Given an overall failure rate of 8%, the conclusion will be that epilation is non-inferior to surgery if the proportion failing in the surgery arm is greater than 4.5%. Epilation will be deemed inferior, if the failure rate in the epilation arm is 15% or higher.

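### Participants last seen without failure and then lost count as 24-month successes in the primary analysis, so the seen-at-least-once rule does not remove the bias towards non-inferiority that it is meant to prevent

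*Protocol*

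**What the plan says.** All references are to the protocol, mainly its Analytical Plan for Trial 2.

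- **Endpoint.** Part a) of the section on the primary outcome gives it as follows: "The primary outcome measure will be the proportion of participants with 5 or more lashes touching the eye on one or more follow-up visits".
- **Estimator.** Part d) of that section reads: "Statistical analyses will calculate the difference in proportion failing in the two arms, and 95%CI for this difference using exact methods". The upper limit must lie below 10% for non-inferiority.
- **Population.** Part e) of that section reads: "Our primary analysis will be a modified intention to treat (ITT) analysis, which will include only those individuals who were seen at least once".
- **Reason given** (also part e)): for trials of this kind the plan warns that "failure to follow people up, biases towards non-inferiority and type I error". It offers the population as its answer to that warning: "in order to prevent bias towards non-inferiority, the primary analysis included only those individuals who were seen at least once".
- **Censoring** (Participant flow, b)): applies to participants who have failed. It sets no rule for those who leave without failing.
- **Visits** (B: Trial Follow-up Phase): both arms are seen at 6, 12, 18 and 24 months. The surgery arm also has a "7-10 day follow-up for surgical patients".
- **Time to event** (f) Secondary analyses): Cox regression of time to first failure, with no link to the 10-point margin.

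**The concern.** The plan identifies the right danger: missed follow-up hides failures, and hidden failures make two arms look alike. Its remedy covers only part of the problem. Dropping those never seen deals with complete loss. Someone seen clear at 6 months and absent at 12, 18 and 24 months stays in the denominator, and any later failure cannot reach the numerator.

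When epilation truly fails more often and loss is similar in the two arms, both proportions shrink by the same factor, and so does their difference. The margin does not shrink with it. The chance of declaring non-inferiority when the true excess is 10 points then rises above its nominal 2.5%. This affects the trial's main claim, and the written rationale tells the reader that the problem has been solved.

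**Working it through.** **1. Reproducing the plan's own figure.** Inputs from c) Sample size: 585 per arm, 5% v 10% failing, margin 10 points, one-sided alpha 0.025.

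- SE = √[(0.05×0.95 + 0.10×0.90)/585] = 0.01533
- Power = Φ[(0.10 − 0.05)/0.01533 − 1.96] = Φ(1.30) = 90.3%, against 90% stated.

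The same Wald form with 585 per arm reproduces the Table 2 intervals to within 0.1 point, so it is a fair tool here.

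**2. Inputs for the check.** From the plan: 1300 recruited (650 per arm), 10% loss over two years, 5% failing with surgery, 10-point margin, visits at 6, 12, 18 and 24 months. Assumed, because the protocol gives no timing: true epilation failure of 15% (the boundary of non-inferiority), with failures and losses spread evenly over the four intervals and unrelated to each other.

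**3. Share of failures captured.** With 10% loss, 2.5% of an arm leaves in each interval. Those leaving in the first are never seen and drop out of the analysis. Those leaving in the second, third and fourth intervals have had 25%, 50% and 75% of their failure risk observed.

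- Captured share = [0.90 + 0.025×(0.25 + 0.50 + 0.75)]/0.975 = 0.9615
- Expected proportions: 5% × 0.9615 = 4.81% and 15% × 0.9615 = 14.42%; difference 9.6 points
- Seen per arm = 650 × 0.975 ≈ 634; SE = √[(0.0481×0.9519 + 0.1442×0.8558)/634] = 0.0163
- P(upper limit < 10 points) = Φ[(0.10 − 0.0962)/0.0163 − 1.96] ≈ 4.2%

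Simulation of the same set-up with Wald limits gives about 4.6%. With no loss it gives about 2.7% rather than 2.5%, because the Wald limit is itself slightly liberal; 2.7% is the fair baseline for simulated figures.

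**4. Other loss patterns, same method.** The loss rates in the last three rows are assumptions, not figures from the protocol.

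| Loss, surgery / epilation | Expected difference (points) | False non-inferiority |
|---|---|---|
| none | 10.0 | 2.5% formula, about 2.7% simulated |
| 10% / 10%, even failures | 9.6 | about 4-5% |
| 10% / 10%, 55% of failures by 6 months | 9.8 | about 3.5% |
| 20% / 20% | 9.2 | about 7-8% |
| 5% / 15% | 9.2 | about 7-8% |
| 15% / 5% | 10.0 | 2.5% formula, about 2.7% simulated |

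The front-loaded row spreads the remaining 45% of failures evenly: [0.90 + 0.025×(0.55 + 0.70 + 0.85)]/0.975 = 0.977.

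The last row shows the break-even. The shrinkage acts on 5% in one arm and 15% in the other, so surgery-arm loss about three times epilation-arm loss cancels the effect.

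**5. A second timing model.** Suppose 585 per arm, everyone seen at 6 months, all 10% lost afterwards, and a share f of failures already visible at 6 months. The observed rate is p×[1 − 0.10×(1 − f)]. The difference is 9.25, 9.5 or 9.75 points for f = 25%, 50% or 75%, and the error rate 6.5%, 4.8% or 3.5%.

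**6. Kaplan-Meier on the simulated data of steps 3 and 4.** The expected difference returns to 10.0 points and the error rate to about 2.7%, the same as with no loss.

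**7. The 7-10 day visit.** If it counted as being seen, surgery patients seen only then would enter as successes. With 585 per arm, and 5% or 10% of the surgery arm in that position, the surgery rate becomes 4.75% or 4.5%, the difference 10.25 or 10.5 points, and the error rate 1.8% or 1.2%.

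**The case against.** Several points on the other side stand.

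- **Not everyone lost is a success.** A reader might infer that anyone seen once and later lost is counted as a success. The endpoint is failure at any follow-up visit, so a person who failed before leaving remains a failure. Only those last seen clear are affected.
- **Direction is conditional.** A reader might infer that the error rate must exceed 2.5%. It need not: 15% v 5% loss cancels the bias, and under the second timing model 20% v 0% reverses it (0.8% at f = 25%). The protocol gives no loss rates by arm.
- **The effect is modest at the planned loss.** The shift is about 0.4 point, and the excess error about 1 to 2 percentage points. The plan specifies exact limits rather than Wald. With a score interval as a stand-in, the comparison is 3.9% with 10% loss against 2.6% with none.
- **Some protection exists.** The flowchart reports follow-up status by arm at each visit, so unequal loss would be visible, and the Cox analysis can censor at loss. But neither gives a risk difference to set against 10 points. Further sensitivity analyses could be in a separate plan, but this document already fixes the primary population, estimator, margin and rationale.
- **The early surgical visit does not add to the bias.** A reader might infer that the surgery-only visit makes the entry rule differ by arm and favours epilation. The protocol does not say whether that visit counts; its findings are described separately, under surgical complications. If counted, it would work against non-inferiority.
- **Kaplan-Meier has its own assumption.** It is unbiased only if loss is unrelated to the risk of failure. If failing epilators leave, it too leans towards non-inferiority.

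**Conclusion.** The point holds in a limited form. The primary analysis treats participants last seen without failure as followed to 24 months, and the justification in e) Primary analysis is wrong to say that the seen-at-least-once rule prevents bias towards non-inferiority. The rule removes one source of that bias and leaves partial loss in place.

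At the planned 10% loss, false non-inferiority is about 4-5% with evenly spread failures and losses, or about 3.5% with early failures, against about 2.7% with no loss. These figures rest on a true 5% v 15%, equal loss in the two arms, and timing that the protocol does not state. The 7-8% figures need loss rates that it does not state either.

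The shift is small but can decide a close result. Table 2 calls 4.5% v 11.5% borderline, with an upper limit of 10.1%. Shrinking that 7-point difference by 0.9615 gives 6.7 points, a move of 0.27 point, more than the 0.1 point by which the limit exceeds the margin. Severity: should-fix.

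**What to change.** 1. Make the primary estimate the difference between arms in 24-month cumulative failure, by Kaplan-Meier or life table over the 6, 12, 18 and 24 month visits. Censor non-failures at their last attended visit, use a Greenwood-based 95% confidence interval, and keep the 10-point rule.
2. Keep the crude proportion among those seen as a supportive analysis.
3. Correct the justification in e) Primary analysis: excluding the never-seen does not deal with partial loss.
4. Add a sensitivity analysis for informative loss, judged against the same margin, for example counting incompletely followed epilation participants as failures.
5. State that being seen at least once refers only to the four visits both arms share, so that the 7-10 day visit does not qualify anyone for the primary population.

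The cost is analysis wording and a slightly wider confidence interval. No extra visits or data are needed.

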Trichiasis (lashes touching the eyeball) causes visual loss through corneal opacification. The purpose of the interventions being compared in this trial is to stop eyelashes touching the eyeball. It is anticipated that some of the patients in the surgery arm of the trial may commence epilation if their surgery fails. From an ophthalmic public health perspective they are ‘successes’ if they successfully prevent eyelashes touching the globe, despite the surgery itself having not been totally successful.

Previous studies have used a cut-off of 5 or more lashes for determining treatment choices (Arch Ophth 2006; 124: 309-314). Similarly, this level has been used in national blindness control programmes (The Gambia) as an indication for surgery.

*c) Sample size*

Our sample size of 1300 trial participants would provide 90% power to detect non-inferiority, assuming 10% loss to follow-up over 2 years, a 5% failure rate in the surgery arm, and non-inferiority margin of 10%. (i.e we would conclude non-inferiority if the upper 95%CI for the observed difference in failure rates was less than 10%)

The power to detect non-inferiority under different assumptions with this sample size is shown in the table below

**Table 1:** Power for detecting non-inferiority under different assumptions with sample size of 585 per arm (1300 recruited, 10% loss to follow-up)

| **Proportion failing in surgery arm (**[figure not shown] | **Proportion failing in epilation arm (**[figure not shown] | **Difference in proportions (**µ) | **Inferiority margin (**Δ) | **Power** |
| --- | --- | --- | --- | --- |
| 2% | 6% | 4% | 8% | 93% |
| 2% | 8% | 6% | 10% | 89% |
| 3% | 6% | 3% | 8% | 98% |
| 3% | 9% | 6% | 10% | 85% |
| 4% | 8% | 4% | 8% | 82% |
| 4% | 8% | 4% | 10% | 99% |
| 4% | 9% | 5% | 10% | 94% |
| 5% | 9% | 4% | 8% | 76% |
| **5%** | **10%** | **5%** | **10%** | **90%** |
| 8% | 11% | 3% | 8% | 83% |
| 8% | 12% | 4% | 10% | 93% |

*d) Statistical analysis*

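### The seen-at-least-once rule reduces the bias towards non-inferiority but does not prevent it, because participants lost after a failure-free visit still count as non-failures to 24 months

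*Protocol*

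**What the plan says.** All of this is in the Analytical Plan inside the Protocol, under Primary outcome.

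- **Outcome, part (a):** "the proportion of participants with 5 or more lashes touching the eye on one or more follow-up visits". The follow-up section of the Protocol schedules full examinations at 6, 12, 18 and 24 months in both arms.
- **Estimator and decision, part (d):** "Statistical analyses will calculate the difference in proportion failing in the two arms, and 95%CI for this difference using exact methods". Non-inferiority is shown if the "upper two-sided 95%CI around the estimated difference in proportions is below 10"%.
- **Analysis set, part (e):** a modified intention-to-treat set, "which will include only those individuals who were seen at least once".
- **Reason given, part (e):** in a non-inferiority trial, "failure to follow people up, biases towards non-inferiority and type I error". The rule is adopted for that reason: "in order to prevent bias towards non-inferiority, the primary analysis included only those individuals who were seen at least once".
- **Sample size, part (c):** 1300 recruited, "assuming 10% loss to follow-up over 2 years", leaving 585 per arm.

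For the primary proportion the plan sets no minimum follow-up, does not require the 24-month visit and does not say how missed later visits are treated. The censoring rule under Participant flow covers only participants who have failed. The one analysis that can censor dropouts is the secondary Cox model in part (f), which has no margin attached.

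**The concern.** The numerator needs an observed failure; the denominator needs only one attendance. Someone examined at 6 months with fewer than 5 lashes touching, and then lost, enters the 24-month comparison as a non-failure although three of the four visits were never observed. This is the mechanism that the plan names as a source of bias towards non-inferiority. Excluding the never-seen removes one part of it and leaves the other.

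The confirmatory error rate is at stake. If unobserved later failures pull both proportions down in a similar ratio, the absolute difference falls in that ratio and its upper limit drops below 10% too often. The sample size adds a tension: it treats the 10% lost as excluded (585 per arm), whereas the analysis rule keeps any of them who attended once.

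**Working it through.** **1. The plan's own figure.** Power = Φ((Δ − µ)/SE − 1.96), with SE = √[(p_S(1−p_S) + p_E(1−p_E))/n]. For 5% v 10%, Δ = 10% and n = 585: SE = 0.01533 and power = 90.3%, against 90% stated. The design reproduces, so the same normal approximation is used below.

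**2. Inputs for the check.**
- From the plan: surgery failure 5%, margin 10 points, four visits, overall loss 10%.
- Assumed: true epilation failure 15% (exactly at the margin), 650 per arm all seen at 6 months, and loss unrelated to outcome. The plan gives neither the timing of loss nor the share of the 10% that is partial, so both are varied.

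**3. Dilution.** Let l be the fraction lost after at least one visit, and g the average share of 24-month failures that have occurred by the last attended visit of those lost. The fraction of failures observed is f = (1 − l) + l·g.
- Failures even over four visits, losses spread equally after visits 1-3: g = (0.25 + 0.50 + 0.75)/3 = 0.50.
- Failures even, all losses after visit 1: g = 0.25.
- Failures front-loaded (50/25/15/10%), losses spread: g = (0.50 + 0.75 + 0.90)/3 = 0.717.

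**4. Chance of declaring non-inferiority at a true 10-point difference.** Example with l = 10%, failures even, losses spread: f = 0.95, so the observed rates are 4.75% v 14.25% and the difference is 9.50 points. SE = √[(0.0475×0.9525 + 0.1425×0.8575)/650] = 0.01605. Φ((0.10 − 0.095)/0.01605 − 1.96) = Φ(−1.648) = 5.0%.

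| Partial loss, each arm | Failures | Losses | f | Observed difference (points) | False non-inferiority |
|---|---|---|---|---|---|
| 0% | any | none | 1.000 | 10.00 | 2.5% |
| 5% | front-loaded | spread | 0.986 | 9.86 | 3.1% |
| 5% | even | spread | 0.975 | 9.75 | 3.5% |
| 5% | even | after visit 1 | 0.963 | 9.63 | 4.2% |
| 10% | front-loaded | spread | 0.972 | 9.72 | 3.7% |
| 10% | even | spread | 0.950 | 9.50 | 5.0% |
| 10% | even | after visit 1 | 0.925 | 9.25 | 6.8% |

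A constant per-visit failure probability instead of even timing gives 4.8-6.7% at 10% loss.

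**5. Loss that differs by arm.** The shortfall in the difference is (1 − g)(p_E·l_E − p_S·l_S). With 15% lost in surgery and 5% in epilation, 0.15×0.05 − 0.05×0.15 = 0. The difference stays at 10.0 points and the error at 2.5%.

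**6. What the rule does remove.** If 10% were never seen and counted as successes, the difference would be 0.9×15 − 0.9×5 = 9.0 points. Excluding them takes that part away.

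**7. Effect near the plan's decision boundary.** Table 2 shows 4.5% v 11.5% with an upper limit of 10.1%. At 585 per arm, 7.0 + 1.96×1.573 = 10.1, so it reproduces. Multiplying both rates by 0.95 gives 4.275% v 10.925%, a difference of 6.65 points and an upper limit of 6.65 + 1.96×1.537 = 9.7%. A result that misses the 10% limit would then meet it.

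**8. The alternative estimator.** In simulation with the same even timing and non-informative loss, a Kaplan-Meier difference with Greenwood limits kept the error at about 3% for 5% and 10% loss. At 5% v 10% with 10% loss its power was about 91%.

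**The case against.** Several counter-arguments are sound.

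- The rule does what it says for people never seen. A reader might infer that it leaves the whole bias in place. It does not.
- A reader might also infer that everyone lost after the first visit is scored a success. Anyone who failed at an attended visit, or who presented after surgery from another provider, remains a failure, and a missed middle visit does not hide a failure seen later.
- The direction is not general. Step 5 shows the bias vanishing when loss is three times heavier under surgery at these failure rates.
- Treating all of the plan's 10% as partial loss is the unfavourable reading. Error rates of 9-16% can be produced with 20% loss, or with 5% v 15% loss against epilation, but nothing in the document supports either.
- The effect on the conclusion is narrow. Table 2 has a half-width near 3.1 points, so non-inferiority needs an observed difference below about 6.9. Undoing a 5% dilution lowers that to about 0.95×10 − 3.1 = 6.4, a window of about 0.5 points.
- Part (d) reports a blinded overall failure rate of 8% at the end of the trial. Follow-up was therefore complete when this text was written, and changing the primary estimator at that stage is more than a change of wording.
- Numbers in follow-up and lost will be shown by arm at each visit, and the Cox model accommodates unequal follow-up.

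These points limit the size of the problem and shape the remedy. They do not rescue the stated justification. Showing the losses does not correct the estimate, the Cox model gives no risk difference to hold against 10%, and an unseen analysis plan cannot excuse a reason that this document states wrongly.

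**Conclusion.** The point holds in a limited form. The rule removes the bias from participants never seen and leaves the bias from partial follow-up, so the claim that it prevents bias towards non-inferiority is wrong; it reduces it. The observed difference shrinks when loss is similar in the two arms or heavier under epilation.

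At the margin, the chance of a false non-inferiority claim is about 3.1-4.2% with 5% partial loss and 3.7-6.8% with 10%, instead of 2.5%. These figures rest on 5% v 15% true failure, 650 per arm seen at 6 months, equal loss that is unrelated to outcome, and assumed timing. Nothing here shows that the trial's conclusion is wrong: the document gives neither the actual losses by visit nor results by arm.

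**What to change.** In parts (d) and (e) of Primary outcome:

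1. Estimate the difference in 24-month cumulative failure by life-table or Kaplan-Meier over the 6, 12, 18 and 24 month visits, with participants leaving the risk set after their last attended visit. Hold its upper 95% limit (Greenwood variance) against the 10% margin.
2. Make this the primary estimate if it is specified before unblinding. Otherwise state it as a sensitivity analysis that non-inferiority must also meet.
3. Report the crude seen-at-least-once proportion alongside.
4. Add a tipping-point check by arm for participants lost without failure, because Kaplan-Meier assumes that loss is unrelated to outcome.
5. In the justification, say that the rule reduces the bias, and name partial follow-up as the part that remains.

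The cost is small. The visits are already scheduled, the interval becomes slightly wider and rests on large-sample theory instead of exact methods, and power at 5% v 10% stays near the planned 90%.
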